### Statistical Analyses

An independent biostatistician will perform statistical analysis. The result of recruitment, the specific reasons for data missing and the distribution of each statistical analysis data set will be described. The primary outcome, the change values of hs-CRP from recruitment to day 7 ± 3, day 14 ± 3 and the day of revascularization, and the secondary outcome, the change scores in five dimensions of SAQ at the same time, are both continuous variables. For comparison between groups, the continuous variables will be described using means ± SD, median, interquartile range, etc., and the Shapiro-Wilk normality test and Levene test for variance homogeneity will be performed. A Student *t* test will be used to compare two groups that have a normal distribution with homogeneous variance, otherwise the Wilcoxon rank-sum test will be used. When some continuous variables are converted into categorical variables, these categorical variables will be described using rates, and the chi-square test or Fisher's exact probability method will be used. For comparison within groups, the paired *t* test or Wilcoxon signed-rank test will be used for continuous variables and the McNemar test for categorical variables. If there are baseline imbalances, Cox regression analysis, logistic regression and multivariate analysis of covariance will be used to adjust confounding variables. The longitudinal data with repeated measures will be analyzed using the linear mixed-effects model to assess associations. The safety analysis will tabulate a detailed description of the adverse reactions, adverse events and serious adverse events and compare the difference in incidence between two groups using Fisher's exact probability method. A difference of *P* < 0.05 at two-tailed test will be considered statistically significant in all analyses. The statistical analyses will be performed using SAS software version 9.4 (SAS Institute, Cary, NC, USA).

After metagenomic sequencing is completed, microbiota community structures will be compared at different taxonomic levels. The abundance and diversity of intestinal flora will be analyzed. The relationship between microbiota composition and clinical outcomes will be investigated using univariate and multivariate linear and nonlinear mixed and regression models. Gene annotation will be conducted to study the function of the intestinal flora.

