### Sample Size Calculation

The sample size was estimated using hs-CRP. Currently, the hs-CRP of NSTEACS decreased from 5.30 mg/L to 3.74 mg/L after 14 days of conventional treatment, with a decline rate of 29.43% (26). The hypothesis is that the treatment group could reduce the hs-CRP of NSTEACS by 35%. With a type I error rate of α = 0.05 and a power of 80% (a type II error rate of β = 0.2), one arm requires a sample size of 27. With a 20% drop-out rate, we have to recruit a total of 66 patients. The following is the formula for calculating sample size (27):

$$\begin{array}{l} \text{n}=2{\left[\frac{\left({\text{u}}_{\alpha }+{\text{u}}_{\beta }\right)}{\delta /\sigma }\right]}^{2}+\frac{1}{4}u_{\alpha }^{2} \end{array}$$

n, is the sample size required in each group, δ = μ_1_-μ_2_, is the difference between means of two groups, σ, is the standard deviation, u_α_ and u_β_ are the values of u corresponding to the test level α and type II error probability β, respectively.

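### The primary outcome covers three hs-CRP time points at an unadjusted 0.05 with no deciding comparison, while the sample size assumes one comparison at 0.05

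*Protocol article*

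**What the plan says.** All references are to the protocol article.

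- **Primary outcome.** Statistical Analyses defines it as "the change values of hs-CRP from recruitment to day 7 ± 3, day 14 ± 3 and the day of revascularization". These are three change scores, listed without ranking.
- **Threshold.** The same section says that a P value below 0.05 "at two-tailed test will be considered statistically significant in all analyses". No hierarchy, joint-success rule or adjustment accompanies this.
- **Between-group test.** The choice between Student's t and its rank-based alternative follows a stated rule, applied after normality and variance checks: the former "will be used to compare two groups that have a normal distribution with homogeneous variance, otherwise the Wilcoxon rank-sum test will be used".
- **Mixed model.** "The longitudinal data with repeated measures will be analyzed using the linear mixed-effects model to assess associations". The article does not say whether this model or the two-group test decides the primary outcome.
- **Sample size.** The Sample Size Calculation takes a control-arm hs-CRP that "decreased from 5.30 mg/L to 3.74 mg/L after 14 days of conventional treatment", assumes a 35% fall on SQSX, and enters one difference δ into a formula with α = 0.05 and 80% power. It does not declare day 14 to be the primary time point.
- **Schedule.** The Abstract, Outcomes Measures and Table 1 place hs-CRP at baseline, day 7 ± 3 and day 14 ± 3. None of them has a measurement on the day of revascularization. Under Intervention, revascularization depends on the patient's condition, so not every participant need have such a value.

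**The concern.** An α of 0.05 in a sample-size formula with one δ describes one test. The analysis section describes up to three tests of the primary outcome, each judged at 0.05, and does not say how they combine into one conclusion. A reader of the final report could not tell whether a significant day 7 result with a null day 14 result is a positive trial.

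The answer has consequences. The Discussion makes further study of MACCE depend on this result, so a false positive would carry forward.

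This is more than detail that an article leaves to its analysis plan. The article itself fixes a three-part primary outcome and a blanket threshold. An analysis plan could restore a 5% error rate only by departing from that wording or adding to it.

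**Working it through.** **1. The plan's own figure**

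- Control change: 5.30 − 3.74 = 1.56 mg/L (29.43%).
- SQSX change: 0.35 × 5.30 = 1.855 mg/L, so δ = 1.855 − 1.56 = 0.295 mg/L.
- Formula: n = 2[(u_α + u_β)/(δ/σ)]² + u_α²/4.

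No value of σ is given, so 27 per arm cannot be reproduced directly. Solving backwards, two-sided (u_α = 1.960, u_β = 0.842), n = 27 gives σ ≈ 0.38 mg/L. Adding 20% gives 27 × 1.2 = 32.4, rounded up to 33 per arm, 66 in total. The missing σ is a separate matter. What counts here is that the calculation has one δ, one α and a 14-day basis.

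**2. Error rate if any significant time point counts as success**

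For k independent tests at 0.05, the chance of at least one false positive is 1 − 0.95^k:

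- k = 3: 1 − 0.8574 = 14.3% (Bonferroni bound 3 × 0.05 = 15%).
- k = 2: 1 − 0.9025 = 9.8%.

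Changes from a shared baseline are correlated. The article gives no correlation, so a range is assumed. For equicorrelated normal test statistics, P(at least one |Z| > 1.96) is:

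| Correlation of test statistics | Three tests | Two scheduled visits |
|---|---|---|
| 0 | 14.3% | 9.8% |
| 0.3 | 13.6% | 9.5% |
| 0.5 | 12.5% | 9.1% |
| 0.8 | 9.8% | 7.8% |
| 0.9 | 8.4% | 7.0% |
| 0.95 | 7.3% | 6.5% |

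As a check, t tests were simulated on changes from a common baseline. There were 27 per arm, the between-visit correlation was 0.3–0.7, and 30–100% of patients had a revascularization-day value. At least one P < 0.05 occurred in 12.5–13.6% of null trials with three tests, and in about 9% with two. This agrees with the 0.5 row. If all visits have equal variance s² and equal correlation ρ, each change has variance 2s²(1 − ρ) and any two changes have covariance s²(1 − ρ), so their correlation is 0.5 whatever ρ is.

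**3. Power if all time points must be significant**

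The error rate is then at most 5%. Suppose each comparison alone had 80% power. Joint power would be 0.8³ = 51% for three independent tests, or 0.8² = 64% for two. It rises with positive correlation but stays below 80% unless the tests coincide.

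**4. Two possible remedies**

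- One primary time point: 5% is restored and 27 per arm stands.
- Bonferroni over three tests (0.05/3 = 0.0167, u_α = 2.394): with σ = 0.38, n = 2[(2.394 + 0.842)/(0.295/0.38)]² + 2.394²/4 ≈ 36.2, so 37 per arm. Kept at 27 per arm, power is about 68%.

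**The case against.** The strongest reply is that the article states no success rule. Inflation follows only if any one time point suffices. If day 14 decides, or if all must be significant, the error does not exceed 5%. The 14-day basis of the sample size also points to day 14. This stands, and it is why the figures here are conditional. It does not remove the problem: day 14 is never declared primary, and the all-required reading gives up the stated power.

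A reader might infer more than the text supports, in four ways:

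- **That the false-positive rate simply is double.** About 10% corresponds to a correlation near 0.8 with three tests and an any-time-point rule. The article states neither the correlation nor the rule.
- **That there are definitely three tests.** The revascularization-day value appears only in Statistical Analyses. If only the scheduled visits are used, the two-test column applies.
- **That the choice among models adds further inflation.** The t test and Wilcoxon test follow a stated rule, the mixed model is not tied to the primary outcome, and covariate adjustment is conditional on baseline imbalance. Nothing in the article allows an extra error to be quantified.
- **That the five SAQ dimensions belong to the same problem.** The SAQ is labelled secondary and the article makes no confirmatory claim for it.

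It can also be said that multiplicity is usually settled in the analysis plan, that the trial is small with a surrogate outcome, and that larger studies are planned. These points bear on how serious the problem is. The conflict between the two sections remains.

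**Conclusion.** The point holds in conditional form. As written, the primary outcome has three components at an unadjusted 0.05 and no deciding comparison, and the sample size was calculated for one comparison. Under an any-time-point rule the primary false-positive rate is about 7–14% with three tests (correlation 0.95 to 0), or about 6–9% with the two scheduled visits (correlation 0.95 to 0.5). Under an all-time-points rule the error is held but the 80% power is not. Only a single named comparison keeps both stated properties, and the article does not name one.

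The structure is plain in the text. The size rests on an assumed correlation and an assumed success rule, so it should be quoted as a range.

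**What to change.** Amend the protocol or analysis plan before unblinding:

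1. Make the between-group difference in hs-CRP change from baseline to day 14 ± 3 the single primary comparison, tested two-sided at 0.05. This matches the basis of the Sample Size Calculation.
2. Name one analysis that produces this result, and label any other analysis of hs-CRP as supportive.
3. Make day 7 ± 3 secondary: either test it only if day 14 is significant, or report it with a confidence interval and no claim.
4. Reconcile Statistical Analyses with Outcomes Measures and Table 1 on the day of revascularization. Remove that change from the primary outcome and, if it is measured, report it descriptively with the number of patients contributing.

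The cost is a change of wording and no additional patients. The sponsor loses the option of claiming success on day 7 or the revascularization day alone. The timing is favourable: Trial Status reports recruitment still open, 20 participants through follow-up and no analysis done, so the choice can still be made without knowledge of results.

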## Methods/Design

### Study Design

The randomized, double-blinded and placebo-controlled trial was endorsed by the Ethics Committee of Xiyuan Hospital, China Academy of Chinese Medical Sciences (Version No. XYYY-ASKY-1.1, January 1, 2021), and registered in the Chinese Clinical Trials Registry (ChiCTR2000029226). Our study conforms to the Helsinki Declaration and the Good Clinical Practice guidelines. It follows the Consolidated Standards of Reporting Trials Extension for Chinese Herbal Medicine Formulas 2017 (CONSORT-CHM Formulas 2017)recommendations and the Standard Protocol Items: Recommendations for Interventional Trials statements (SPIRIT) (20, 21). The study is currently underway at the Xiyuan Hospital, China Academy of Chinese Medical Sciences. Altogether 66 participants will be enrolled and randomly allocated to two groups. All participants will receive their respective interventions for 14 days. The clinical evaluations will be conducted at baseline (Visit 1), days 7 ± 3 (Visit 2) and 14 ± 3 (Visit 3), respectively. Figure 1 depicts a schematic of the study design.

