### Inclusion Criteria

Subjects who meet all of the following criteria are eligible to participate in the study: (1) diagnosed as unstable angina (UA) or non-ST segment elevated myocardial infarction (NSTEMI) according to the 2015 ESC guidelines for the management of NSTEACS (22); (2) diagnosed as the TCM syndrome of Qi deficiency and blood stasis according to the Guiding Principles For Clinical Research Of New Chinese Medicines (23); (3) age 40–60 years; (4) heart function is Killip grade I-II for subjects diagnosed as NSTEMI; (5) in-hospital patients; (6) written informed consent is obtained.

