### Intervention

All participants will be randomly allocated to one of the following two groups. Participants in the SQSX group will receive conventional treatment plus SQSX, while the placebo group will receive conventional treatment plus placebo, both for 14 days. The conventional treatment is based on the NSTEACS guideline issued by the European Heart Association in 2015 (22), including but not limited to the following: (1) anti-myocardial ischemic drugs: isosorbide mononitrate 20mg twice daily; (2) platelet inhibition: aspirin 100 mg once daily and ticagrelor 90 mg twice daily; (3) anticoagulation: enoxaparin 1 mg/kg s.c. twice daily; (4) invasive coronary angiography and revascularization according to the practical condition; (5) high-intensity statin therapy: atorvastatin 40 mg po qn. The composition and daily dosage of SQSX equal to Huangqi (Astragali Radix) 50 g, Danggui (Angelicae Sinensis Radix) 10 g, Danshen (Salviae Miltiorrhizae Radix Et Rhizoma) 30 g, Ezhu (Curcumae Rhizoma) 20 g, Huanglian (Coptidis Rhizoma) 10 g and Baizhu (Atractylodis Macrocephalae Rhizoma) 10 g. The placebo is made up of 5% granule and 95% dextrin with a look, smell and taste similar to active granule. Both SQSX and placebo (both 10 g per bag) are produced by Beijing Kangrentang Pharmaceutical Co., Ltd. (Beijing, China) in full accordance with the standards of Chinese Pharmacopeia and Good Manufacturing Practice. They use the same package with the study name and drug number printed on the surface. Subjects will be told to mix the granules with 100 mL of boiled water until dissolved and to drink it 30 min after breakfast and dinner. (10 g at a time, twice a day). To ensure adherence, study medicine will be distributed and/or retrieved at each visit.

During the study period, the use of any other Chinese medicine for the treatment of CAD is forbidden. Antibacterial drugs, probiotic drugs, proton pump inhibitors, immunosuppressants, hormones, drugs for gastrointestinal diseases, and drugs with a direct effect on intestinal flora are not permitted.

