### Outcomes Measures

The primary outcome, hs-CRP, and secondary outcome the SAQ will be assessed at baseline, 7 ± 3 days and 14 ± 3 days. At all visit windows, other indicators including creatine kinase (CK), creatine kinase-myocardial band (CK-MB), cardiac troponins I (cTnI), 12-lead electrocardiograph and the syndrome scores of Qi deficiency and blood stasis will be tested and metagenomic sequencing for intestinal flora will be performed (25). Echocardiography and safety assessment will be performed at baseline and 14 ± 3 days. All adverse events will be tracked throughout the study. Table 1 lists the items measured as well as the data collection window.

**Table 1 T1:** Data collection items and measurement points.

	**Screening**	**Treatment period**		
	**(Visit 0)**	**D1** **(Visit 1)**	**D7 ± 3** **(Visit 2)**	**D14 ±3** **(Visit 3)**

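### The analysis section adds the day of revascularization to the primary and secondary outcomes, but no visit is scheduled for it and only a subset of patients can have a value

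*Protocol article*

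**What the plan says.** The Statistical Analyses section of the protocol article defines the primary outcome as "the change values of hs-CRP from recruitment to day 7 ± 3, day 14 ± 3 and the day of revascularization"; the words at issue are "day 14 ± 3 and the day of revascularization". It gives the secondary outcome the same times: "the change scores in five dimensions of SAQ at the same time". The between-group comparison is a t test or, if its assumptions fail, a rank-sum test: "A Student *t* test will be used to compare two groups that have a normal distribution with homogeneous variance".

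The other sections give a shorter list. Outcomes Measures states: "The primary outcome, hs-CRP, and secondary outcome the SAQ will be assessed at baseline, 7 ± 3 days and 14 ± 3 days". The abstract agrees. Study Design states: "The clinical evaluations will be conducted at baseline (Visit 1), days 7 ± 3 (Visit 2) and 14 ± 3 (Visit 3), respectively". Table 1 marks hs-CRP and SAQ at Visits 1, 2 and 3; it has no column for a revascularization day and no event-triggered visit.

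The Intervention section lists, as part of the conventional treatment for both groups, "invasive coronary angiography and revascularization according to the practical condition". The diagnostic entry criterion is "diagnosed as unstable angina (UA) or non-ST segment elevated myocardial infarction (NSTEMI)", and no inclusion criterion requires revascularization.

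**The concern.** The article states its primary outcome in two ways that do not agree. One version has two post-baseline time points, both scheduled for everyone. The other has a third, tied to a procedure that only some patients undergo, on a day that differs between patients.

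Two things are at stake. First, a site that follows the printed schedule may not have hs-CRP or SAQ on the procedure day. Second, even if samples are taken, the comparison is restricted to patients who were revascularized, and they will have taken study drug for different lengths of time. If treatment influences who is revascularized or when, the two subsets are no longer comparable by randomisation. All tests use P < 0.05 and the section names no time point as decisive, so a result on this subset could be presented as a primary finding.

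**Working it through.** **1. Time points side by side (hs-CRP and SAQ).**

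| Place in the protocol article | Baseline | Day 7 ± 3 | Day 14 ± 3 | Day of revascularization |
|---|---|---|---|---|
| Abstract | yes | yes | yes | no |
| Study Design (visits) | yes | yes | yes | no |
| Outcomes Measures | yes | yes | yes | no |
| Table 1 | yes | yes | yes | no |
| Statistical Analyses | reference for change | yes | yes | **yes** |

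The fourth column appears in one place only.

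**2. Can the schedule supply the value by chance?** The Visit 2 window runs from 7 − 3 = 4 to 7 + 3 = 10. The Visit 3 window runs from 14 − 3 = 11 to 14 + 3 = 17. Together they cover days 4 to 17, so a procedure in that period may coincide with an assessment. Nothing makes it coincide, and days 2 and 3 lie outside both windows.

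**3. Who has a value, and after what exposure?** The procedure is discretionary and not required for entry, so patients who are never revascularized have no value, and the article assigns them none. Its timing relative to randomisation or first dose is not stated. If it follows the first dose, exposure at measurement differs by patient. If it falls on or before the first dose, the change contains no treatment effect.

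**4. Effect size implied by the planned sample size.** Sample Size Calculation gives n = 2[(u_α + u_β)/(δ/σ)]² + u_α²/4, with α = 0.05, power 80% and n = 27 per arm. It gives no value for σ, so 27 cannot be reproduced forward. Solving for δ/σ with two-sided u_α = 1.960 and u_β = 0.842:

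- u_α²/4 = 0.960
- δ/σ = (1.960 + 0.842) / √[(27 − 0.960)/2] = 2.802 / 3.608 = 0.776

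A one-sided u_α = 1.645 would give 0.685 instead. The analysis section specifies two-tailed tests, so 0.776 is used below.

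**5. Power in a revascularized subset (illustration).** Two-sample t test, two-sided 0.05, noncentral t with 2n − 2 degrees of freedom and noncentrality 0.776 × √(n/2). The revascularized shares are assumptions; the article gives no rate.

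| Assumed share | Patients per arm (of 27) | Power |
|---|---|---|
| 100% | 27 | about 80% |
| 70% | 18.9, taken as 19 | about 64% |
| 50% | 13.5, taken as 14 | about 51% |
| 30% | 8.1, taken as 8 | about 30% |

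A normal approximation at the unrounded subset sizes gives somewhat higher values (about 67%, 52% and 35% for the three subsets); the pattern is the same.

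**6. Selection bias (illustration).** This simulation assumes no true effect on hs-CRP. Treatment lowers the revascularization rate from 50% to between 31% and 40%, and the tendency to be revascularized correlates 0.2 to 0.4 with hs-CRP change. The subset comparison is then off by about 0.03 to 0.14 SD. If treatment does not affect who is revascularized, the bias is zero. All inputs here are assumed.

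**The case against.** The strongest reply is that this is one inconsistent phrase in a condensed article. Day 7 and day 14 are scheduled consistently everywhere, and the sample size rests on the 14-day change, so the main comparison is untouched. The full protocol may provide for an event-triggered sample that a fixed-day table has no natural place for. The trial is double-blind, which limits differential decisions to revascularize.

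Much of this stands, and it rules out some stronger readings that a reader might infer:

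- *No patient will have the measurement.* Not supported. The windows cover days 4 to 17 and may coincide with a procedure; the schedule merely does not guarantee a value.
- *The comparison is biased.* Not shown. Bias requires treatment to change who is revascularized or when, and its size is unknown. Blinding reduces the risk but does not remove selection through a treatment effect on symptoms, and the Discussion itself expects SQSX to ease short-term symptoms.
- *The subset is certainly selected after randomisation.* This is an inference from the procedure's place within the treatment of the randomised groups; the article gives no timing.
- *The trial's effect size is 0.78 SD.* The article states no SD. The figure is back-solved, and it carries a 14-day effect over to what may be a shorter exposure.
- *Revascularized patients are dropped from the day-14 comparison.* Nothing in the article says so.

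What the reply does not remove is the contradiction in the definition of the primary outcome, or the fact that any value on the procedure day is confined to a subset with varying exposure. Adding a sample to the schedule would cure the first problem but not the second.

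**Conclusion.** The point holds as an internal contradiction in the primary and secondary outcome definitions, with a consequence for the analysis. The day of revascularization is a stated time point without a scheduled measurement, and it can be observed only in a discretionary subset. A between-group test there would have less power than the planned comparison: about 30% to 64% for assumed shares of 30% to 70%, against about 80% with all 27 per arm, given the back-solved 0.776 SD. It would also carry a risk of selection bias whose size the article does not allow one to determine. The contradiction rests on the text alone; the power and bias figures are illustrations. The day-7 and day-14 comparisons are unaffected. It needs correcting because it concerns the primary outcome.

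**What to change.** By a documented amendment made before any analysis, reconcile Statistical Analyses with Outcomes Measures and Table 1: take the day of revascularization out of both the hs-CRP and the SAQ outcome definitions. Record the date of revascularization. Report any hs-CRP or SAQ values from that day as descriptive or exploratory only, with the number of patients contributing in each arm.

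The cost is the amendment itself. The trial is registered, ethics-approved and recruiting, so a change to a stated primary outcome needs a dated record and a reason. Trial Status reports 20 participants through follow-up and no analysis yet, so on that account the change can still precede any look at the data. No scheduled data are lost, and the 14-day premise of the sample size and the total of 66 are unchanged.

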## Discussion

Based on our previous pharmaceutical studies, SQSX shows a good pharmacological effect of neovascularization and preventing in-stent restenosis. In clinical practice, it's also widely prescribed as a complementary medicine for CAD. Therefore, we would like to initiate a randomized, double-blind, placebo-controlled trial to examine the efficacy and safety of SQSX for NSTEACS. ACS is usually accompanied by gastrointestinal ulcers or bleeding (28, 29), and long-term use of antiplatelet drugs or combined use of multiple anticoagulant drugs causes gastrointestinal mucosal damage (30, 31). These pathological states of the intestinal mucosal barrier cause translocation and disturbance of intestinal flora (32). The disturbed intestinal flora and its metabolite TMAO are one of the reasons that promote the progression of CAD (12, 33, 34). As is well known, NSTEACS is at a critical stage from stable to unstable, which is likely to be accompanied by significant changes in the intestinal flora. We consider that SQSX could be an effective intestinal flora regulator, helping to ease the short-term symptoms of NSTEACS by improving intestinal flora disturbances and gastrointestinal tract injury. The study is possible to provide evidence for the use of intestinal flora modifiers in the treatment of ACS. The above hypotheses are still unclear, so we intend to verify in this trial.

There are three limitations to this work. First, the sample size of the study is small and might be biased. Therefore, two subsequent clinical studies with a larger sample size (*n* = 120) will be launched this year as a follow-up supplement. Second, the biomarker hs-CRP is observed as a surrogate indicator for the incidence of MACCE and does not yet fully explain the efficacy. We'll determine whether or not to investigate the incidence of MACCE further according to the result. Third, we only control the effects of combined medications on the intestinal flora, and could hardly standardize the patient's eating habits and other multivariate factors that affect intestinal flora. We will educate patients and document their dietary and lifestyle habits to ensure consistency of multiple factors as much as possible.

To conclude, the purpose of the trial is to examine the efficacy and safety of SQSX for NSTEACS and explore the possible pharmacological mechanisms.

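### The one named secondary outcome, the SAQ, is tested as five dimension scores at up to two scheduled visits, each at P < 0.05, with no leading comparison, adjustment or exploratory label

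*Protocol article*

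**What the plan says.** The Outcomes Measures section treats the SAQ as one outcome, and it is the only one called secondary: "The primary outcome, hs-CRP, and secondary outcome the SAQ will be assessed at baseline, 7 ± 3 days and 14 ± 3 days". The enzymes, troponin, electrocardiograph and syndrome scores are listed as other indicators. Table 1 likewise schedules the SAQ at baseline and at the two follow-up visits.

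The Statistical Analyses section divides that outcome into five variables: "the secondary outcome, the change scores in five dimensions of SAQ at the same time, are both continuous variables". The phrase about the same time points back to the times listed for the primary outcome, "the change values of hs-CRP from recruitment to day 7 ± 3, day 14 ± 3 and the day of revascularization".

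Continuous variables are compared between arms by a Student t test where the distribution allows: "test will be used to compare two groups that have a normal distribution with homogeneous variance, otherwise the Wilcoxon rank-sum test will be used". The decision rule is general: "A difference of *P* < 0.05 at two-tailed test will be considered statistically significant in all analyses". The section also plans a linear mixed-effects model for repeated measures, but does not say whether it replaces the visit-by-visit tests or adds to them.

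The article names no leading SAQ dimension, summary score or visit. It gives no order of testing and no adjustment, and does not call the SAQ exploratory.

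**The concern.** A reader of the outcome list expects one secondary result for angina symptoms. The analysis text produces five to ten, each judged at 0.05 on its own. The dimensions may disagree with each other, and day 7 may disagree with day 14. Nothing in the article says which result answers the question.

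This matters because the primary outcome is a biomarker. The Discussion accepts that hs-CRP is a surrogate and does not fully explain efficacy, so readers will look to the SAQ for the result closest to the patient. With several unadjusted tests and no leading one, a chance finding in one dimension at one visit can be reported as significant under the stated rule.

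The article is not merely silent here. It fixes 0.05 for every analysis, so a later document that adjusted the SAQ comparisons would have to depart from it.

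**Working it through.** **Inputs from the article**
- Level: 0.05, two-tailed, for every analysis (Statistical Analyses).
- SAQ variables: 5 dimension change scores (Statistical Analyses).
- Scheduled follow-up times for the SAQ: 2, at days 7 ± 3 and 14 ± 3 (Outcomes Measures and Table 1).

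**Inputs assumed**
- Correlation between dimensions 0 to 0.7, and between visits 0 to 0.8. The article gives neither.

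The article states no error rate for the SAQ as a whole, so there is no figure of its own to reproduce.

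**Number of between-arm tests**
- Visit by visit: 5 × 2 = 10.
- One treatment effect per dimension from the mixed model: 5 × 1 = 5.

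Within-arm tests are not counted.

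**Independent tests, no treatment effect**
- Any P < 0.05, either direction: 1 − 0.95^k. For k = 5 this is 1 − 0.7738 = 0.226. For k = 10 it is 1 − 0.5987 = 0.401.
- At least one significant result favouring SQSX: 1 − 0.975^k. For k = 5 this is 0.119. For k = 10 it is 0.224.

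**Correlated tests, no treatment effect**

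Each comparison is drawn as a standard normal statistic (200,000 draws per setting). The correlation between two different dimensions at two different visits is the product of the two assumed correlations. A draw counts if any |z| > 1.96 (either direction) or any z > 1.96 (benefit).

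| Tests | Between dimensions | Between visits | Either direction | Benefit |
|---|---|---|---|---|
| 5 | 0.5 | – | 0.183 | 0.091 |
| 5 | 0.7 | – | 0.148 | 0.074 |
| 10 | 0.3 | 0.5 | 0.354 | 0.183 |
| 10 | 0.5 | 0.5 | 0.312 | 0.156 |
| 10 | 0.5 | 0.7 | 0.288 | 0.145 |
| 10 | 0.7 | 0.8 | 0.222 | 0.110 |

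Over the whole range, from independence to the strongest correlations tried:
- Five tests: about 15% to 23% in either direction, 7% to 12% for benefit.
- Ten tests: about 22% to 40% in either direction, 11% to 22% for benefit.

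**After the fix**
- One named dimension at one visit: 5% two-sided, so 2.5% in the direction of benefit.
- Holm across five dimensions at one visit: the smallest P is compared with 0.05/5 = 0.01. With no effect on any dimension and independent tests, the chance of any false rejection is 1 − 0.99^5 = 0.049. Positive correlation lowers it.

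**The case against.** The strongest reply is that this is a secondary outcome in a condensed article. Multiplicity for secondary outcomes is often settled in the analysis plan, and a closing sentence on P < 0.05 is a common convention. This stands in part: the absence of a full multiplicity section would be no finding. But the article goes further. It divides its one secondary outcome into five variables and applies 0.05 to all of them.

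A second reply is that the mixed model may reduce the count. This stands, and it is why five tests are shown beside ten. The article does not say which analysis decides. Five unadjusted tests still give 15% to 23%.

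Several stronger readings are tempting, but the article does not support them:
- **A false claim of benefit is six times as likely as the stated 5%.** About six times is the either-direction figure for ten tests at correlations of 0.5 (0.312/0.05 = 6.2). In the direction of benefit the chance is 0.156, about three times 5%. It is six times only against the 2.5% that one two-sided test allows in that direction.
- **The plan breaks a promised 5% rate.** The 5% is a per-test level. No family-wise rate is promised for the SAQ, and nowhere does the article say that one significant dimension would establish symptom benefit. The problem is that no rule prevents that reading.
- **There are fifteen tests.** That count needs an SAQ on the day of revascularization, which Outcomes Measures and Table 1 do not schedule. Revascularization also depends on the patient's condition, so not every patient would have that time point. The listed times need reconciling, but they should not enlarge this point.
- **The Discussion commits the trial to an SAQ claim.** It speaks of "helping to ease the short-term symptoms of NSTEACS by improving intestinal flora disturbances and gastrointestinal tract injury", but as something the granule could do, as part of an intestinal-flora hypothesis, and without naming the SAQ.

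**Conclusion.** The point holds at moderate size. The single named secondary outcome is up to ten between-arm comparisons, or five under one reading of the mixed model, each called significant at 0.05 with nothing to say which one counts. If any significant SAQ comparison were read as a symptom effect, the chance of at least one false positive in either direction would be about 15% to 23% (five tests) or 22% to 40% (ten). About half of that favours SQSX.

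These ranges rest on the assumed correlations and on that way of reading the results. They do not touch the type I error of the primary hs-CRP comparison. The change should be made, but the defect does not threaten the trial's main result.

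**What to change.** In Statistical Analyses, before unblinding, do one of the following:
- name one SAQ dimension at day 14 ± 3 as the secondary comparison, tested at two-sided 0.05; or
- apply Holm across the five dimensions at day 14 ± 3.

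Report the other SAQ dimensions and times as exploratory, with estimates and 95% confidence intervals. Limit the sentence on P < 0.05 in all analyses to match. State whether the mixed model or the t/Wilcoxon test decides the SAQ comparison.

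Do not make the SAQ test conditional on a significant hs-CRP result. The article names no deciding time for hs-CRP, so that condition would be undefined, and tying a symptom outcome to a biomarker is a trade-off this point does not need.

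The cost is one or two sentences, with no new data or patients. Fewer SAQ results could then be called significant. Trial Status reports 20 participants through follow-up and no analysis yet, so the choice can still be made independently of the results.
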